### Analyses of primary and secondary outcomes

The primary outcome will be analyzed with logistic regression models to evaluate the association between sociotherapy and the 30-day readmission rate. This model will be adjusted for potential confounders as described below. Both ITT and PPA will use the same statistical models for the analysis. However, since the magnitude of the odds ratios estimated in logistic regression model cannot be compared across models, we can only compare whether the effects are positive or negative [12, 13].

For the secondary outcome 365-day readmission to psychiatric hospitalization, we will apply the same procedure as for the primary outcome 30-day readmission. Regarding time to first psychiatric readmission, we will generate cumulative incidence curves to illustrate the time to readmission for participants in both the intervention and control group. The log-rank test will be employed to compare the distributions. Further, we will use Cox-regression models to account for confounders. The secondary outcome total number of psychiatric hospitalizations within a 365-day period and cumulative number of days spent in the hospital due to psychiatric admissions we will apply Poisson regression models. In cases where overdispersion is detected, we will instead use negative binomial regression models. If a high prevalence of zero counts is observed, we will address this by applying zero-inflated Poisson or zero-inflated negative binomial regression models. Both ITT and PPA will be applied to all secondary outcomes.

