Follow-Up Period	Starts at randomization and ends 30 days/365 days after discharge of the index event, death, or loss to follow-up	Starts at the last day of the index event and ends 30 days/365 days after discharge of the index event, death, or loss to follow-up
Outcome	Primary outcome • Readmission to hospital for psychiatric treatment within 30 days after discharge Secondary outcomes • Readmission to hospital for psychiatric treatment within 365 days after discharge • Time to first psychiatric rehospitalization • Total number of rehospitalizations within 365 days after discharge • Cumulative number of days spent in the hospital due to psychiatric admissions during 365 days after discharge	Primary outcome • Readmission to hospital for psychiatric treatment within 30 days after discharge Secondary outcomes • Readmission to hospital for psychiatric treatment within 365 days after discharge • Time to first psychiatric rehospitalization • Total number of rehospitalizations within 365 days after discharge • Cumulative number of days spent in the hospital due to psychiatric admissions during 365 days after discharge
Causal Contrasts Of Interest	• Intention-To-Treat (ITT): The ITT evaluates the average treatment effect among the treated (ATT), regardless of whether the patients adhered to the treatment • Per-Protocol (PPA): The PPA evaluates the average treatment effect among the treated (ATT), accounting for the non-adherence to the sociotherapy treatment in the intervention group, and usage of sociotherapy in the control group due to prescriptions of sociotherapy unrelated to the assignment procedure	• Intention-To-Treat (ITT): The ITT evaluates the average treatment effect among the treated (ATT), regardless of whether the patients adhered to the treatment • Per-Protocol (PPA): The PPA evaluates the average treatment effect among the treated (ATT), accounting for the non-adherence to the sociotherapy treatment in the intervention group, and usage of sociotherapy in the control group due to prescriptions of sociotherapy unrelated to the assignment procedure

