### Outcomes

The primary outcome is the average treatment effect among the treated (ATT) on the 30-day readmission rate to a psychiatric hospital. A readmission is defined as a subsequent admission to an inpatient setting for patients who were previously discharged from an inpatient setting. For patients who received the index treatment in an inpatient-equivalent setting, a readmission includes admission to inpatient, or inpatient-equivalent setting. For patients who received the index treatment in a semi-inpatient setting, a readmission includes admission to any of these levels of care: inpatient, semi-inpatient, or inpatient-equivalent. However, a transfer between these settings is not considered a readmission but rather a continuation of the index event, provided that the transfer occurs on the same day. In addition to the primary outcome, we define the following secondary outcomes: the ATT on 365-day readmission rate for psychiatric hospitalization, the ATT on time to first psychiatric readmission, the ATT on total number of psychiatric hospitalizations within a 365-day period, and the cumulative number of days spent in the hospital due to psychiatric admissions during this time frame.

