### Confounders

In all multivariate analyses, we will adjust for key characteristics of the index event, including the PEPP category, the length of the index event, diagnoses of index event (dementia, substance abuse, schizophrenia and schizoaffective disorder, bipolar disorder and manic episodes, major depressive disorder, post-traumatic stress disorder, and personality disorder), the necessity for intensive treatment (OPS-Code 9–61), whether the admission was an emergency admission, other prescribed or certified DM measures (medication, remedies and aids, home care, outpatient intensive care specialized outpatient palliative care, patient transportation, digital health applications, and incapacity certificate). We will also control for participants' medical history prior to the index hospitalization, as such previous psychiatric hospitalizations, comorbidities in form of the Elixhauser Comorbidity Index [14] and care level. As for demographic variables, we will include age, sex, population density at the place of residence and the German Index of Socioeconomic Deprivation [15] (Table 2).

**Table 2 Tab2:** Variables

Category	Variable	Operationalization
Exposure	Sociotherapy	Prescription of Sociotherapy as a DM measure (ITT) / Prescription of Sociotherapy as a DM and utilization of at least one sociotherapy session (PPA)
Index event	PEPP	PO/PP/PA/TP/QA
	Length of index event	Number of days of index event
	Dementia	F00.x– F03.x, G30.x
	Substance abuse	F10.2, F11.2, F12.2, F13.2, F14.2, F15.2, F16.2, F17.2, F18.2, F19.2
	Schizophrenia & Schizoaffective disorder	F20.x, F21.x; F25.x
	Bipolar disorder & Manic episodes	F30.1– F30.2, F31.1– F31.2, F31.4- F31.6
	Major depressive disorder	F32.2– F32.3; F33.2– F33.3
	Post-traumatic stress disorder	F43.1
	Personality disorder	F60.x– F61.x
	Intensive treatment	OPS 9–61
	Emergency admission	Reason for admission
Discharge management measures (presciptions and certificates)	Medication	
	Remedies and aids	
	Home care	
	Outpatient intensive care	
	Specialized outpatient palliative care	
	Patient transportation	
	Digital health applications	
	Incapacity certificate	
Medical history	Elixhauser Comorbidity Index [16]	Based on all available diagnoses twelve months prior to the index event
	Number of psychiatric hospital days	Hospital stays with PEPP categories PO, PP, PA, TP & QA based on all available data twelve months prior to the index event
	Care level	Based on care level on the last day prior to the index event

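### The plan names the ATT on the 30-day readmission rate as its primary quantity but estimates a covariate-adjusted odds ratio, and for that reason allows ITT and per-protocol effects to be compared only by sign

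*Protocol article*

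**What the plan says.** **Estimand.** The Outcomes section states: "The primary outcome is the average treatment effect among the treated (ATT) on the 30-day readmission rate to a psychiatric hospital". Table 1 (Design section) makes the ATT the causal contrast for both analyses. For ITT: "The ITT evaluates the average treatment effect among the treated (ATT), regardless of whether the patients adhered to the treatment". For per-protocol: "The PPA evaluates the average treatment effect among the treated (ATT), accounting for the non-adherence to the sociotherapy treatment in the intervention group".

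**Estimator.** The section Analyses of primary and secondary outcomes specifies the model as follows: "The primary outcome will be analyzed with logistic regression models to evaluate the association between sociotherapy and the 30-day readmission rate". It adds shortly after: "This model will be adjusted for potential confounders as described below". The Confounders section opens "In all multivariate analyses, we will adjust for key characteristics of the index event" and goes on to discharge measures, medical history and demographic variables, which Table 2 lists. This adjustment comes on top of propensity score matching or weighting (Assignment procedures).

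**Comparison rule.** The same analysis section says "Both ITT and PPA will use the same statistical models for the analysis". It then observes that the size of odds ratios cannot be compared between models, and concludes that "we can only compare whether the effects are positive or negative". The 365-day readmission outcome follows the same procedure.

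**The concern.** An ATT on a rate is a contrast of two risks in one population: the readmission risk of the treated patients with sociotherapy, and the risk the same patients would have had without it. The coefficient of a covariate-adjusted logistic model is a log odds ratio within covariate strata. It depends on which covariates are in the model, it is not the average of anything over the treated, and it does not determine the change in the rate. The article contains no step that turns the model output into risks.

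Two things are at stake. The quantity named as primary would not be what the described analysis delivers. And the article gives up any comparison of size between its two causal contrasts, although two ATTs on a rate share a scale. The Conclusion says the results may inform insurance coverage, and readers in that setting may take an odds ratio for a risk reduction.

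**Working it through.** **1. The plan's own figures.** The article gives no risk difference, risk ratio or odds ratio to reproduce. Its only figures for the primary outcome are the sample sizes 449 (10% baseline) and 329 (20%). Both reproduce as numbers per arm under assumed two-sided alpha 0.05, 80% power, 1:1 allocation and pooled variance, with effect size 0.3 read on the probit scale: p1 = Φ(Φ⁻¹(p0) + 0.3), so 10% goes to 16.3% and 20% to 29.4%. The present point does not change them.

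**2. Estimand against estimator.**

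| | Estimand (Outcomes, Table 1) | Analysis (Analyses, Confounders) |
|---|---|---|
| Scale | Readmission rate | Odds |
| Type | Average over the treated | Conditional on the Table 2 covariates |
| ITT against per-protocol | Common scale, sizes comparable | Sign only |

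**3. How far one odds ratio fixes the change in rate.** All inputs here are assumptions. The conditional odds ratio is 0.58. The covariates enter as a score L, normal with mean 0 and SD s on the log-odds scale, with s from 0 to 1.5. The control risks are 10% and 20% (the baselines used in the sample size section) and 40% for 365 days (not in the documents).

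Model: logit P(Y=1 | A, L) = a + ln(0.58)·A + L. Choose a so that the average risk with A=0 equals p0, then average the risk with A=1 over L to get p1. The risk difference is p1 − p0 and the risk ratio p1/p0.

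For s = 0 this can be done by hand:
- p0 = 10%: odds 0.1111 × 0.58 = 0.0644; p1 = 0.0644/1.0644 = 6.05%; difference -3.9 points.
- p0 = 20%: odds 0.25 × 0.58 = 0.145; p1 = 0.145/1.145 = 12.7%; difference -7.3 points.
- p0 = 40%: odds 0.6667 × 0.58 = 0.3867; p1 = 0.3867/1.3867 = 27.9%; difference -12.1 points.

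For s > 0 the average is taken by numerical integration:

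| Control risk | s | p1 | Risk difference (points) | Risk ratio | Marginal odds ratio |
|---|---|---|---|---|---|
| 10% | 0 | 6.05% | -3.9 | 0.61 | 0.580 |
| 10% | 1.5 | 6.61% | -3.4 | 0.66 | 0.637 |
| 20% | 0 | 12.7% | -7.3 | 0.63 | 0.580 |
| 20% | 1.5 | 14.1% | -5.9 | 0.71 | 0.658 |
| 40% (assumed, 365 days) | 0 | 27.9% | -12.1 | 0.70 | 0.580 |
| 40% (assumed, 365 days) | 1.5 | 31.1% | -8.9 | 0.78 | 0.677 |

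**4. Reading.** The same conditional odds ratio corresponds to different effects on the rate, depending on baseline risk and on how prognostic the covariates are. A reader who takes 0.58 as a 42% risk reduction would be facing a true reduction of 34% to 39% at 10% risk, 29% to 37% at 20%, and 22% to 30% at 40%.

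**The case against.** **Matching or weighting already targets the treated.** Matching controls to the treated would set the right population, and adjusting the outcome model afterwards is accepted practice. That stands. But the adjustment makes the coefficient conditional again, so it is still not the ATT on a rate.

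**Standardisation may be left to a fuller analysis plan.** It may, and its absence from an article alone would be no finding. The sign-only rule is different: it is a stated decision, and it would contradict an analysis that standardised both effects.

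**The planned cumulative incidence curves show absolute risks.** They serve the secondary time-to-readmission outcome and do not supply an adjusted ATT for the primary one.

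**The gap is small for the primary outcome.** This stands for low risks and weakly prognostic covariates: at 10% risk the whole assumed range spans about half a percentage point.

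Some stronger readings are tempting but not supported:
- *That only the direction of each effect will be reported.* The sentence limits comparison between models. It does not forbid reporting the size of each effect, and its caution about odds ratios is statistically sound.
- *That a common scale would show how far non-adherence dilutes the effect.* The per-protocol population is selected on behaviour after baseline, so the ITT and per-protocol difference mixes dilution with selection on any scale.
- *That the adjusted model is badly overfitted.* The stated sample sizes are a minimum for going ahead, not the expected sample, and they reproduce per arm: about 449 × (0.100 + 0.163) = 118 and 329 × (0.200 + 0.294) = 163 events. Unstable coefficients for rare covariates depend on prevalences that the article does not give.

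**Conclusion.** The point holds as a mismatch between the stated estimand and the stated analysis, with a comparison rule that follows only from the effect measure chosen. As written, the analysis does not deliver the ATT on the readmission rate for ITT, per-protocol or 365-day readmission.

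The practical size is modest at 30 days and larger at 365 days. These figures rest on the assumed odds ratio, the assumed spread of the covariate score and, for 365 days, an assumed 40% risk. The mismatch itself rests only on the article's text. It should be corrected before analysis. It does not make the adjusted odds ratio invalid as a secondary summary, and it does not show the treatment estimate to be unstable.

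**What to change.** - Make the primary result the marginal risk difference, with the risk ratio beside it, in the treated. From the matched or ATT-weighted outcome model, predict each treated patient's 30-day risk with and without sociotherapy and average both over the treated.
- Use bootstrap or sandwich intervals that respect the matching or the weights.
- Report the same measure for ITT, per-protocol and 365-day readmission. Keep the odds ratios as secondary.
- Replace the sign-only sentence. Say that the standardised effects are on one scale and can be set side by side, but that ITT and per-protocol concern different populations, so their difference does not by itself measure dilution.

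This needs no new data: the models already planned supply the predictions. The cost is a little extra code and a few sentences of text.

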Analysis Plan	• Logistic regression models for the primary outcome readmission to hospital for psychiatric treatment within 30 days after discharge and the secondary outcome readmission to hospital for psychiatric treatment within 365 days after discharge • Cumulative incidence curves and a log-rank test, as well as Cox-regression models for the outcome time to first psychiatric treatment • Poisson Regression (or negative binominal regression) for the outcomes total number of hospitalizations within 365 days after discharge and cumulative number of days spent in the hospital due to psychiatric admissions during 365 days after discharge	• Logistic regression models for the primary outcome readmission to hospital for psychiatric treatment within 30 days after discharge and the secondary outcome readmission to hospital for psychiatric treatment within 365 days after discharge • Cumulative incidence curves and a log-rank test, as well as Cox-regression models for the outcome time to first psychiatric treatment • Poisson Regression (or negative binominal regression) for the outcomes total number of hospitalizations within 365 days after discharge and cumulative number of days spent in the hospital due to psychiatric admissions during 365 days after discharge

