### Follow-up period

We follow up with participants for 30 days after discharge to assess the primary outcome, and for up to 365 days for secondary outcomes, or until death—whichever occurs first. During the follow-up period, we will evaluate the continuation of sociotherapy prescriptions as a component of a structured DM, as well as any new prescriptions issued in the outpatient setting.

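### The zero-inflated fallback for the two count outcomes can yield an effect that is not the declared ATT on 365-day totals, and Table 1 does not list it

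*Protocol article*

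**What the plan says.** The target is set in two places of the Protocol article. The Outcomes section lists "the ATT on total number of psychiatric hospitalizations within a 365-day period, and the cumulative number of days spent in the hospital" among the secondary outcomes. Table 1, under Design, gives the causal contrast for the study as a whole: "The ITT evaluates the average treatment effect among the treated (ATT), regardless of whether the patients adhered to the treatment". The per-protocol contrast in the same table is also an ATT. So both count outcomes are to be read as effects on a 365-day total among treated patients.

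The section Analyses of primary and secondary outcomes then gives three steps for these two outcomes:

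- Start: "cumulative number of days spent in the hospital due to psychiatric admissions we will apply Poisson regression models" (the same sentence covers the number of hospitalizations).
- First switch: "In cases where overdispersion is detected, we will instead use negative binomial regression models".
- Second switch: "If a high prevalence of zero counts is observed, we will address this by applying zero-inflated Poisson or zero-inflated negative binomial regression models".

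The analysis row of Table 1 covers the same outcomes more narrowly: "Poisson Regression (or negative binominal regression) for the outcomes total number of hospitalizations within 365 days after discharge", and likewise for the days. It has no zero-inflated model.

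**The concern.** Every patient who is not readmitted within the year contributes a zero to both outcomes, so the zero-inflated branch may well be used, although the article gives no 365-day readmission rate. A zero-inflated model splits the outcome into a latent class that can only be zero and a latent susceptible class with its own count distribution. Its count coefficient compares the arms within the susceptible class. If treatment also enters the zero part, a second coefficient gives an odds ratio for belonging to the always-zero class. Neither is in general the effect on the mean total among the treated.

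The trigger is also a poor one. A large share of zeros does not by itself indicate zero inflation, because a low mean or overdispersion produces many zeros too. The step from a mean model to a latent-class model could therefore be taken for a reason that does not justify it, after the outcome data have been seen.

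At stake is whether the two utilisation outcomes give one interpretable answer. If the count coefficient carries the conclusion, a real fall in mean hospital days can read as no effect, and an unchanged mean can read as an increase.

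**Working it through.** The article states no rate, zero share, dispersion or power for the count outcomes, so there is no figure of its own to reproduce. All numerical inputs below are assumptions chosen to show the mechanism.

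**Algebra.** Let π be the structural-zero probability and μ the mean in the susceptible class, with subscript 1 for treated and 0 for control.

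- Poisson and negative binomial: both model log E[Y], so exp(β) = E[Y₁]/E[Y₀], a ratio of means.
- Zero-inflated models: E[Y] = (1 − π)μ. The count coefficient gives μ₁/μ₀; the ratio of means is (1 − π₁)μ₁ / ((1 − π₀)μ₀). They agree only if π₁ = π₀.

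**Worked case.** π₀ = 0.6, π₁ = 0.7, μ = 30 days in both arms.

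- Control mean: 0.4 × 30 = 12.0 days.
- Treated mean: 0.3 × 30 = 9.0 days.
- Ratio of means: 9.0/12.0 = 0.75; difference: 3.0 days fewer per treated patient.
- Count-part ratio: 30/30 = 1.00.
- Odds ratio for a structural zero: (0.7/0.3)/(0.6/0.4) = 1.56.

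**Simulation check.** 100,000 patients per arm, no covariates, dispersion 0.8 for days in scenario C. A and B are hospitalizations; C to E are days.

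| | π₀, π₁ | μ₀, μ₁ | True mean ratio | Poisson | Neg. binomial | ZIP count ratio | ZINB count ratio | ZIP inflation OR | ZIP standardised to means |
|---|---|---|---|---|---|---|---|---|---|
| A | 0.6, 0.7 | 1.5, 1.5 | 0.75 | 0.751 | 0.751 | 1.005 | 1.005 | 1.57 | 0.751 |
| B | 0.6, 0.7 | 1.5, 2.0 | 1.00 | 1.006 | 1.006 | 1.340 | no usable fit | 1.55 | 1.006 |
| C | 0.6, 0.7 | 30, 30 | 0.75 | 0.758 | 0.758 | 1.004 | 1.004 | 1.53 | 0.758 |
| D | 0.6, 0.7 | 30, 40 | 1.00 | 1.012 | 1.012 | 1.331 | 1.338 | 1.52 | 1.012 |
| E | 0.6, 0.6 | 30, 24 | 0.80 | 0.800 | 0.800 | 0.805 | 0.801 | 1.01 | 0.800 |

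The true ratios follow from the formula; for D, for example, (0.3 × 40)/(0.4 × 30) = 12/12 = 1.00.

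Three results follow. Poisson and negative binomial agree in every scenario. The zero-inflated count ratio departs from the mean ratio in A to D and matches it in E, where treatment leaves the zero part alone. Predicting E[Y] under each treatment from the fitted ZIP model and taking the ratio returns the Poisson value in all five.

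**Treatment left out of the zero part.** A ZIP model with a constant inflation term gave count ratios of 0.879 (A), 1.215 (B), 1.004 (C), 1.331 (D) and 0.805 (E). Omitting treatment from that part does not restore the mean ratio where treatment in fact changes the zero share.

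**Zeros without zero inflation.** Take the control mean of scenario A, 0.4 × 1.5 = 0.6 hospitalizations. A plain Poisson outcome with that mean has exp(−0.6) = 55% zeros. A negative binomial with dispersion 0.8 has (1 + 0.8 × 0.6)^(−1/0.8) = 1.48^(−1.25) = 61% zeros. Neither has a latent always-zero class.

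**The case against.** The strongest reply is that the article never says a raw zero-inflated coefficient will be reported as the treatment effect. It declares the ATT as target, and a standardised zero-inflated model delivers a mean contrast, as the last column of the table shows. The model sequence is conventional and announced in advance, and an article may leave the details to an analysis plan that is not shown. This stands in part: zero-inflated models do not rule out the ATT. But the article states both the ATT target and the zero-inflated fallback and does not link them, and its own table describes a different set of models. That is a matter of what is published, not of detail left out.

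A reader might infer more than this. These stronger readings are not supported:

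- That moving from Poisson to negative binomial also changes the effect measure. It does not; both target the ratio of means, and the switch alters the variance model.
- That standard errors for hospital days will be far too small. The stated switch to negative binomial under overdispersion already addresses this.
- That the lack of numerical thresholds for overdispersion or for many zeros, or of a rule between the two zero-inflated models, is itself a defect. Such detail commonly sits in an analysis plan.
- That the ITT and per-protocol analyses will end on different models. Nothing says that selection is done separately, and the article says that the two use the same models, though in the paragraph on the primary outcome.
- That an effect through the zero part would go unseen. It would show in the inflation coefficient, and 365-day readmission is a secondary outcome in its own right.

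The numerical example is also a chosen case that puts the whole effect in the zero part. Scenario E shows no discrepancy when the zero share is equal.

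**Conclusion.** The point holds in a limited form. For two secondary outcomes, the stated rule can lead to a model whose count coefficient is not the declared estimand, on a trigger that does not by itself justify that model, and Table 1 does not list it. Under the assumed inputs the count coefficient reads about 1.00 when the mean falls by 25%, and about 1.33 when the mean is unchanged. How large the gap would be in these data cannot be said, since it depends on the unknown zero share in each arm and on whether treatment alters it. The article does not show that the wrong quantity will be reported; it leaves that open. The primary outcome, the sample size and the rule for discontinuing the emulation are untouched.

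**What to change.** Name one effect measure for both count outcomes: the ratio and the difference of mean 365-day totals among the treated. Estimate it with a log-link Poisson quasi-likelihood model in the matched or ATT-weighted sample, with sandwich or bootstrap standard errors. Given a correctly specified mean, this stays valid under overdispersion and many zeros, so no data-driven switch is needed.

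Do not use a log follow-up offset by default. The outcome is a 365-day total, and an offset would turn it into a rate per time at risk. Continuous insurance through December 2024 is an eligibility condition, and follow-up runs "for up to 365 days for secondary outcomes, or until death", so it should vary little except through death.

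Keep negative binomial or zero-inflated models as sensitivity analyses, each standardised to the same mean contrast by averaging predictions under both treatments over the treated patients. Then make the analysis row of Table 1 and the section Analyses of primary and secondary outcomes list the same models.

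The cost is a change of wording and simpler code. The downside is a slight loss of efficiency if a negative binomial model were exactly true.
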